**Figure 2 Fig2:**
[figure not shown]
Cascade safety monitoring procedures.

### Assessments

#### Feasibility

The feasibility of Cascade will be determined by recording the (i) time taken to recruit sufficient participant numbers, (ii) proportion of participants who required loaned technology, (iii) time taken to complete and return questionnaires, (iv) study response rate (feasible at 40%), (v) attrition rates of each arm (feasible at 20%), and (vi) proportion of children who participate. Feasibility will also be assessed by examining the flow-through of the study (from opt-in to final questionnaire completion), using medians and ranges.

#### Demographic measures

Table 1 summarises the planned assessments. Information on parent age, sex, education, employment status, and family structure will be collected, as well as information on the child’s diagnosis and treatment regimen using standardised items adapted from the Childhood Cancer Survivor Study [52]. Information such as whether the child relapsed or received a bone marrow transplant will be obtained. This data will be sufficient for a qualified paediatric oncologist to grade the child’s treatment intensity according to the validated Treatment Intensity Scale [53] will be included in order to assess the severity/intensity of the child survivor’s medical treatment. Information on the gender and age of all child participants will be obtained. Parent participants will also be asked to report on all forms of psychological support accessed at each time point.

#### Parent/caregiver psychosocial functioning

There is little consensus regarding the relative superiority of generic versus disease-specific psychosocial measures in psycho-oncology. Disease-specific measures often appeal to researchers due to the difficulty ascertaining ‘clinical’ change in populations that may only be distressed at sub-clinical levels [54,55]. However, generic psychological measures facilitate comparison to healthy norms, which can be clinically and empirically advantageous [56]. As such, the Cascade trial uses both generic and disease-specific indicators of psychosocial functioning.

The Pediatric Quality of Life inventory (PedsQL) Family Impact Module [57] was selected as the primary psychosocial outcome variable as it assesses parent/caregiver functional concerns specifically related to their child’s illness. Four purposefully developed and pilot-tested items were also added to specifically index parents’ concerns (if any) about their child’s cancer recurring. The widely-used EQ-5D-5 L [58] is a generic measure that will assess parents’ wellbeing in five domains: mobility, self-care, engagement in usual activities, physical pain/discomfort and anxiety/depression.

The Psychosocial Adjustment to Illness Scale-Interview Form (PAIS) [40] will be administered over the telephone. The PAIS assesses adjustment of patients and parents/carers to illness across seven domains: health care orientation, vocational environment, domestic environment, sexual relationships, extended family relationships, social environment and psychological distress.

The Parent Self-Agency Measure (Revised) [59] provides an index of parents’ general confidence in their parenting behaviours. Parenting competence is of interest in Cascade due to its bi-directional relationship with child development and adjustment outcomes. Importantly, parents’ confidence in their ability to parent and associated positive parenting practices may be a protective factor for families under stress [60].

Finally, items from the Patient-Reported Outcomes Measurement Information System (PROMIS) short-form questionnaires will be used to assess depression and anxiety symptomology. PROMIS has excellent psychometric properties superior to many other measures available to assess emotional functioning [61].

#### Child psychosocial functioning

The Paediatric Quality of Life Inventory (PedsQL) Generic Core [62] parent proxy-report scale will be used to assess the cancer survivor’s quality of life in physical, emotional, social, and school-related domains of functioning. In a recent review of QoL measures for children, the PedsQL emerged as a feasible and valid tool that is widely used in cancer and chronic disease [63]. All participating children (the child survivor and/or any siblings) will also complete a child self-report version of the scale.

#### Intervention engagement and impact

To assess participants’ mood in a more dynamic manner across the intervention, parents will complete the Emotion Thermometers Tool [39] each week, 24-hours prior to participating in their weekly session (Cascade or PSG). At the same time, parents will complete the 6-point Homework Compliance Scale [64] to assess compliance with the home practice exercises. CBT skills used will also be assessed using 10 purposely developed and pilot-tested items; for example, assessing participants’ ability to ‘recognise unhelpful thoughts and how they are making me feel’ (response options range from ‘not at all’ to ‘a lot’). The Working Alliance Inventory - Short (WAI- S) [65] and The California Psychotherapy Alliance Scale - Group (CALPAS-G) [66] will be used to assess participants’ perceptions of the therapeutic working alliance, during and after the intervention.

#### Satisfaction with intervention

After participating in Cascade or the PSG, parents will provide ratings of specific intervention elements to determine their acceptability. Open-ended questions will also be used to elicit views about the benefit and/or burden of participating and suggestions for improvement.

### Data management and analysis

All measures (excluding the PAIS telephone interview) will be administered online through Key Survey (WorldAPP, Braintree, MA, USA) at all time points, unless paper versions are requested by participants. Key Survey enables participants’ data to be securely downloaded to files amenable to statistical analysis using the Statistical Package for the Social Sciences, version 18.0 (SPSS, Inc., Chicago, IL, USA).

#### Statistical analyses

This trial will employ ‘intention-to-treat’ and ‘as-treated’ analyses. Analyses will be based on mixed random-intercept models that will assess differences between the groups in terms of change in QoL from T1 to T2 (the primary analysis), from T1 to T3, and from T1 to T4. Random intercept models, which utilise maximum-likelihood estimation, provide more efficient estimates of effects with unbalanced data than the traditional repeated measures approach [67]. Multiple regression analyses will be conducted using T1 data to identify demographic and other factors that contribute to treatment outcome. Multiple comparisons will be used to test a priori hypotheses and to conduct post-hoc testing, with the alpha rate adjusted using the Holm-Bonferroni method [68].

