Evidence-based psychological interventions have the potential to reduce parental mental health burden in the ‘coming off treatment’ phase, thus curtailing longer-term difficulties. Best-practice interventions target modifiable processes associated with parents’ poor adaptation to their child’s cancer. For example, parents of children with cancer can use more ruminative thinking and defensive coping strategies [13], both of which can create conflict and poor family cohesion [25]. Interventions that increase parents’ use of adaptive coping strategies in the face of their child’s cancer may reduce their risk of depression and anxiety [26] and enhance their parenting skills [17]. Improving parents’ communication skills can also promote adaptive functioning in children with cancer [27]. Parents’ capacity to proactively solve problems and seek help when needed is also modifiable, yielding improved outcomes for children with cancer when targeted [13,28].

Skills-based interventions can be effective in parents of children with cancer, yielding medium-large effects [29]. However, few interventions have been rigorously evaluated. Most are also implemented face-to-face, limiting benefits to rural and remote families. It is clear that online cognitive-behavioural therapy (CBT) programs can be effective, with meta-analyses reporting medium-large effects for anxiety [30] and depression [31]. Trans-diagnostic programs that target co-morbid anxiety and depression may also be effective when delivered online [32]. Online programs also have the potential to reduce distress and improve wellbeing in those who care for someone with a medical condition [33]. Furthermore, group-based support is cost-effective and provides a unique context in which individuals can provide each other with emotional support, reflect on the commonalities of their experiences, and share resources [34]. Given that no efficacious, online programs currently exist to provide support for Australian parents at this recognised critical adjustment period [35], we developed a tailored intervention, ‘Cascade’, to meet their needs.

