### Participants

This study will recruit 120 parents (approximately 40 in each arm). This sample size will allow medium-to-large differences in parent QoL to be detected with a power of 80% at a two-tailed significance level of 0.05 (assuming Cohen’s d = 0.65 as the difference in change from time 1 to time 2 for any pair of groups, standardised on the pooled within-group standard deviation). This effect size is clinically significant [38]. It is anticipated that approximately 375 parents will need to be approached to achieve a final sample of 120 participants (assuming a 40% response rate and 20% attrition rate).

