Participants randomised to Cascade will participate in four, live, weekly, 90-minute sessions facilitated by a psychologist. Each group will comprise a psychologist and three to five participants with mixed cancer experiences (such as the age of their child and their child’s type of cancer). Participants also receive a purposely developed workbook, outlining the content of each session, providing additional examples and suggesting ‘homework’ activities to facilitate skill development. Additional files 2, 3 and 4 show details of the workbook content and graphic design.

Sessions will be delivered through WebEx (Cisco WebEx, USA). WebEx requires a computer with standard browser, a high-speed internet connection, and a webcam. WebEx is a secure, password-protected video-conferencing program that allows up to six participants to be seen on the screen simultaneously, similar to group Skype™. Participants will receive a reminder text message on their cellular phone 24 hours before their session, which will also serve as their reminder to complete the Emotion Thermometers Tool [39] and homework compliance scale (see *Assessments*).

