#### Peer-support group (active control)

The PSG control is delivered in an identical manner to Cascade (via WebEx, up to five participants per group), with the same frequency of contact (four weekly 90-minute sessions) and availability of peer-based group discussion. The PSG is delivered by the same facilitator as Cascade (see *Treatment fidelity* for further discussion). Like Cascade, it also involves supportive counselling to normalise the range of parent experiences and provides parents an opportunity to give and receive emotional/practical support. During each session, parents are encouraged to exchange information about a nominated topic (matched to those addressed in Cascade for example, ‘relationships and social support’). The key distinction between Cascade and the PSG is that the PSG does not include directive, structured teaching of specific, CBT-based coping skills. The PSG in this trial will adhere to best practice guidelines [50] and is manualised to ensure standardisation across all sessions.

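### Cascade and PSG run in small live therapy groups, but the sample size assumes independent parents and the primary model names no therapy-group term; if outcomes correlate within groups, Cascade–PSG precision and power are overstated

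*Protocol article*

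**What the plan says.** In this note, 'arm' means a randomised arm and 'therapy group' means the parents who meet together. The article uses 'group' for both.

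- **Delivery.** Parents are randomised individually (Randomisation). For Cascade, "Each group will comprise a psychologist and three to five participants" (Interventions, Cascade). PSG is run the same way, with "up to five participants per group" (Peer-support group). Waitlist parents receive no group programme until after the 6-month wait.
- **Peer interaction.** The Background says that group-based support "provides a unique context in which individuals can provide each other with emotional support". Table 2 and the PSG section make peer discussion a component of both active arms.
- **Sample size (Participants).** "This study will recruit 120 parents (approximately 40 in each arm"), "with a power of 80% at a two-tailed significance level of 0.05", taking d = 0.65 "as the difference in change from time 1 to time 2 for any pair of groups", "standardised on the pooled within-group standard deviation". No ICC, therapy-group size or design effect is given.
- **Model (Statistical analyses).** "Analyses will be based on mixed random-intercept models that will assess differences between the groups", with T1-to-T2 change in quality of life as the primary analysis. The random intercept is justified by comparison with traditional repeated-measures analysis. No group-level term, clustering or robust error appears.

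**The concern.** The design is partially nested: two arms are clustered by therapy group and one is not. Parents who share four live sessions share the same discussion, so their changes may be alike. The article itself gives reasons for therapy groups to differ. Its Discussion expects that PSG members may raise coping skills spontaneously, and that the facilitator's practice may change over the study.

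If such correlation exists, a model with only a parent-level intercept treats 40 parents in 8 to 15 therapy groups as 40 independent units. The contrast most exposed is Cascade versus PSG, where both arms are clustered. It is one of the two efficacy hypotheses and tests whether skills training adds anything to peer support. Each waitlist contrast has one clustered arm, so the error differs by contrast. The Holm-Bonferroni adjustment does not correct for it.

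**Working it through.** **1. Reproduce the plan's figure.** Inputs from Participants: d = 0.65, two-sided alpha 0.05, power 80%, independent parents.
- Normal approximation: n = 2 × ((1.960 + 0.842)/0.65)² = 37.2, so 38 per arm. The two-sample t version gives 38.1, so 39.
- Power at 40 per arm is 81.9% (t) or 82.8% (normal).
- Attrition is already covered: 375 × 0.40 × 0.80 = 120.

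The stated 40 is therefore the independent-parents answer plus one or two parents. That leaves no real allowance for clustering.

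**2. Number of therapy groups.** Participant recruitment gives five blocks of about 30 opt-ins, or about 10 per arm per block. That makes two groups of 5 or three groups of 3–4, hence 10–15 groups per arm. With 40 per arm after attrition the mean is 40/15 = 2.7 to 40/10 = 4. If groups are kept at the maximum of 5, there are 40/5 = 8 per arm.

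**3. Effect on Cascade–PSG.** The ICC of change is assumed, because the article gives none. Formulas:
- design effect DE = 1 + (m − 1) × ICC, with effective n = 40/DE;
- standard error in SD units = √(2 × DE/40);
- type I error when the groups are ignored = 2 × (1 − Φ(1.96/√DE));
- 'design effect only' power: two-sample t with 40/DE per arm;
- 'group-level df' power: noncentral t with 2 × (40/m − 1) df.

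Example with m = 4 and ICC = 0.10: DE = 1 + 3 × 0.10 = 1.30; effective n = 30.8; 1.96/√1.30 = 1.719, so type I error is 8.6%.

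| Mean m (groups per arm) | ICC | DE | 40/DE | Type I error, groups ignored | Power, design effect only | Power, group-level df |
|---|---|---|---|---|---|---|
| 2.7 (15) | 0.02 | 1.03 | 38.7 | 5.4% | 80.6% | 78.8% |
| 2.7 (15) | 0.05 | 1.08 | 36.9 | 6.0% | 78.7% | 76.9% |
| 2.7 (15) | 0.10 | 1.17 | 34.3 | 7.0% | 75.6% | 73.8% |
| 4 (10) | 0.02 | 1.06 | 37.7 | 5.7% | 79.6% | 76.1% |
| 4 (10) | 0.05 | 1.15 | 34.8 | 6.8% | 76.2% | 72.7% |
| 4 (10) | 0.10 | 1.30 | 30.8 | 8.6% | 70.8% | 67.4% |
| 5 (8) | 0.02 | 1.08 | 37.0 | 5.9% | 78.8% | 73.9% |
| 5 (8) | 0.05 | 1.20 | 33.3 | 7.4% | 74.3% | 69.4% |
| 5 (8) | 0.10 | 1.40 | 28.6 | 9.8% | 67.5% | 62.8% |

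Simulating a t-test that ignores groups of 4 gave 6.7% and 8.5% at ICC 0.05 and 0.10, in line with the formula. At ICC 0.01 and m = 4 the type I error is 5.3%.

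**4. Waitlist contrasts.** Here the standard error is √(DE/40 + 1/40). With m = 4, power by the normal approximation is 80.1% at ICC 0.05 and 77.4% at ICC 0.10, against 82.8% with no clustering.

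**5. Which random effect is needed.** Baseline is collected before the sessions, so a therapy-group effect arises after T1. A group intercept that is constant over time enters T1 and T2 equally and cancels from the difference. With change variance 1, the standard error of the arm-by-time contrast is √(2/40) = 0.2236 with or without such an intercept. A post-baseline group effect that takes 10% of that variance, with groups of 4, gives √(2 × 1.30/40) = 0.2550.

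**The case against.** **The direction is conditional.** Nothing in the article shows a positive ICC for change over the four-week programme. One facilitator leads both arms and PSG is manualised, which removes between-facilitator variance. The Background remark on mutual support is general, and the article derives Cascade's mechanisms from CBT. This stands: the point holds only if the ICC is positive. It does not dispose of the concern, because a shared facilitator does not remove differences between peer groups.

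**The model half is an inference.** The article never states the level of the random intercept, and an analysis plan that is not shown may include a therapy-group term. This also stands, although the contrast with repeated measures points to the parent. Such a plan would not repair the power stated in Participants.

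**Part of the power loss is not clustering.** With 10 groups per arm and an ICC of zero, a group-level test on 18 df already has 78.5% power. So 81.9 − 78.5 = 3.4 points of the fall come from degrees of freedom. The two power columns above keep these apart.

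**Stronger readings.** A reader might infer that the errors are certainly wrong, or that the trial is too small and must recruit more. The documents do not support either. There is no ICC to fix the size; with 15 groups per arm and ICC 0.02, power from the design effect alone is still 80.6%. Nor does the article rank Cascade–PSG above the waitlist contrasts, which are less affected.

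**Conclusion.** The point holds in conditional form and should be fixed; it does not invalidate the design. The sample-size part is firm, since 40 per arm reproduces as an independent-parents figure. The model part rests on reading the random intercept as parent-level.

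If the within-group ICC of T1-to-T2 change is positive, standard errors for Cascade–PSG are too small, those for the waitlist contrasts less so, and power is below the independent-parents figure. For ICC 0.02–0.10 and a mean of 2.7–5 parents per group, both assumed, the type I error for Cascade–PSG is about 5.4%–9.8%. Power at d = 0.65 is about 81%–68% from the design effect alone and 79%–63% with group-level degrees of freedom. At ICC 0.01–0.02 the effect is small. It becomes material from about 0.05.

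**What to change.** 1. Record a therapy-group identifier for every Cascade and PSG parent.
2. For the T1-to-T2 contrast, state a therapy-group random effect that acts on change. Use either a post-baseline (group-by-time) random effect in the longitudinal model, or a T2 model adjusted for T1 (or a change-score model) with a therapy-group random effect. A time-constant group intercept is not enough, for the reason in step 5 of the working.
3. Apply it in the Cascade and PSG arms only. Treat waitlist parents as singletons without group variance, and use Satterthwaite or similar small-sample degrees of freedom.
4. In Participants, restate power for Cascade–PSG and for the waitlist contrasts over a stated range of ICC and group size, keeping the 120 parents.

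The cost is one extra data field and a few lines of text. Intervals become slightly wider and the stated power less favourable. The model should be settled before outcomes are seen by arm, because adding the term later would be harder to defend.

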### Randomisation

Participants will be randomised to one of the three arms using a flexible biased urn method of randomisation, which adapts to the degree of imbalance between groups in a dynamic manner over the trial [41]. This method is superior to standard stratification in balancing groups across multiple covariates [42,43], whilst also being a suitable method when groups remain small [41,44,45]. The groups will be balanced across two factors: i) severity of distress as measured by the Emotion Thermometers Tool [39] and ii) degree of rural/remoteness as assessed by the Accessibility/Remoteness Index of Australia [46]. An independent researcher will electronically randomise participants to treatment group.

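### The primary contrast is stated as a difference in T1–T2 change with no baseline adjustment or common T1 mean, which costs precision but not validity

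*Protocol article*

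**What the plan says.** Under Statistical analyses: "Analyses will be based on mixed random-intercept models", fitted by maximum likelihood, which will "assess differences between the groups in terms of change in QoL from T1 to T2 (the primary analysis"). Changes from T1 to T3 and from T1 to T4 follow. No covariate is named for these models. T1 data appear as predictors only in a separate exercise: "Multiple regression analyses will be conducted using T1 data to identify demographic and other factors that contribute to treatment outcome".

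Two other places bear on how the model is parameterised. The opening of Methods/Design crosses the three arms with all four assessments, T1 included, as one factorial layout. The sample-size paragraph under Participants takes "d = 0.65 as the difference in change from time 1 to time 2 for any pair of groups", standardised on a pooled within-group SD. It does not say whether that SD is of the change or of the raw score.

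Under Randomisation, allocation is made "using a flexible biased urn method of randomisation, which adapts to the degree of imbalance between groups". The factors are Emotion Thermometers distress severity and remoteness: "The groups will be balanced across two factors". Neither is mentioned in the analysis text.

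**The concern.** In a randomised trial the arms have equal expected QoL at T1, so any observed T1 difference between arms is chance. A change-score contrast subtracts that chance difference in full. A baseline-adjusted contrast subtracts only the part that predicts T2, and its variance is never larger. A random-intercept model does not secure this gain by itself: if T1 is an outcome with a separate mean in each arm, the arm-by-time contrast reduces to the difference in mean change.

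Precision is at stake in a trial where parents are the scarce resource. The article expects to approach 375 to obtain 120, and its Discussion accepts that three arms will lengthen recruitment. The T1 score is already collected from everyone.

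**Working it through.** **Inputs from the article.** d = 0.65 on the difference in change; 40 per arm; two-sided 0.05; 80% power; 40% response; 20% attrition.

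**Assumed, because the article gives no value.** T1–T2 correlation ρ from 0.4 to 0.8; equal SDs at T1 and T2; d standardised on the SD of change.

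**1. The plan's own figures.** The normal formula gives 38 per arm and the two-sample t test gives 39, or 117 in total against 120. Power at 40 per arm is 82.8% (normal) or 81.9% (t). Recruitment: 375 × 0.40 × 0.80 = 120. The stated size reproduces on the change-score scale.

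**2. Variance ratio.** Per parent:

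- Change score: 2σ²(1 − ρ)
- Baseline-adjusted: σ²(1 − ρ²)
- Ratio, adjusted to change: (1 − ρ²) / [2(1 − ρ)] = (1 + ρ)/2

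At ρ = 0.4 the ratio is 1.4/2 = 0.70. The standard error is multiplied by √0.70 = 0.837, a cut of 16%. Power is recomputed with d/√ratio in the t test.

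| ρ (assumed) | Variance saving | CI-width saving | Power, 40 per arm, 0.05 | Per arm for 80% power |
|---|---|---|---|---|
| change score | – | – | 81.9% | 39 |
| 0.4 | 30% | 16% | 92.9% | 28 |
| 0.5 | 25% | 13% | 91.2% | 29 |
| 0.6 | 20% | 11% | 89.4% | 31 |
| 0.7 | 15% | 8% | 87.6% | 33 |
| 0.8 | 10% | 5% | 85.7% | 35 |

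Put another way, 40 parents per arm with adjustment are worth 40/0.70 = 57 at ρ = 0.4 and 40/0.90 = 44 at ρ = 0.8.

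**3. Multiplicity.** The two QoL hypotheses imply three pairwise contrasts. If these form the Holm family, its first step tests at 0.05/3 = 0.0167. Power there rises from 67.7% to 84.5%, 78.7% and 73.0% at ρ = 0.4, 0.6 and 0.8. Only the smallest p-value faces that level; later steps use 0.025 and 0.05.

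**4. Does the random-intercept model already give the gain?** Simulation of three arms of 40, T1 and T2 only, complete data, 150 runs per setting. Mean standard error of one arm contrast:

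| Model | ρ = 0.4 | ρ = 0.6 | ρ = 0.8 |
|---|---|---|---|
| Raw change | 0.2398 | 0.1973 | 0.1399 |
| Random intercept, T1 means free by arm | 0.2398 | 0.1973 | 0.1399 |
| Same, plus both factors as main effects | 0.2398 | 0.1973 | 0.1399 |
| Random intercept, common T1 mean | 0.2022 | 0.1772 | 0.1329 |
| T2 regressed on arm and T1 | 0.2047 | 0.1766 | 0.1333 |
| Same regression, plus both factors | 0.2007 | 0.1735 | 0.1323 |

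With free T1 means the mixed model matches raw change. With a common T1 mean it recovers the whole gain. The two factors do nothing as main effects in the free-mean model and lower the reported standard error by about 1–2% in the baseline-adjusted one. The run-to-run spread of the adjusted estimates did not clearly fall when they were added (0.2065 to 0.2091, 0.1762 to 0.1764, 0.1354 to 0.1344). The simulation assumed a distress–QoL correlation of 0.4–0.5 and balanced on distress strata only, not with the urn itself.

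**The case against.** The strongest reply is that the article leaves the parameterisation open. A random-intercept model that targets change from T1 is also what a common-T1-mean model does, and a condensed article may leave mean structure and covariates to the analysis plan. This stands in part: the text does not rule out the better model. But the factorial layout and the powering on difference in change make free T1 means the natural reading, and nothing stated points the other way.

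Four stronger readings are tempting and not supported:

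- A reader might infer that the baseline score is ignored. It is not; T1 enters the contrast as a repeated outcome. It is only used inefficiently if its mean is free by arm.
- A reader might infer that leaving out the balancing factors makes the standard errors too wide and the test conservative. Time-constant effects of distress and remoteness cancel from within-person change, and step 4 shows identical standard errors with and without them. They matter only so far as they predict change, and the article gives no information on that.
- A reader might quote the 10–30% as a known loss of precision. It is a variance saving that rests wholly on an assumed correlation; interval width changes by 5–16%.
- A reader might infer bias or an invalid test. A randomised change-score comparison is unbiased with a valid type I error rate, and the planned 120 meets its stated power at 0.05 on that scale.

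**Conclusion.** The point holds as one of efficiency. As most naturally read, the primary contrast is as imprecise as raw change, and using the T1 score would lower its variance by a factor of (1 + ρ)/2: 30% at ρ = 0.4 down to 10% at ρ = 0.8, with power at 0.05 going from 82% to between 93% and 86%.

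The direction does not depend on the assumptions, but the size does. If d was meant on the SD of the raw score, the variance ratio is unchanged and the power figures move. If the full analysis plan already uses a common T1 mean or adjusts for T1, the loss disappears and only the wording needs attention. The balancing factors are a secondary matter with a small expected gain.

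**What to change.** Prespecify, before any unblinded analysis, that the primary model is a longitudinal mixed model with a common T1 mean across the three arms, free arm means at T2 to T4, and the arm difference at T2 as the primary contrast. Include distress severity and remoteness category with factor-by-time terms, or as covariates in a baseline-adjusted model; main effects alone in a free-mean model achieve nothing.

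Prefer the constrained mixed model to a regression of T2 on arm and T1. The two agree closely with complete data, but the regression drops parents with no T2 score, whereas the mixed model keeps them, and the article expects 20% attrition.

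The constraint requires T1 to be measured before allocation. The article places the first questionnaire at the time of the intake call and allocation after the intake interview, which fits; the plan should say so outright. The cost is a sentence or two, with no new data and no change to the trial's conduct.

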This study employs a three (treatment condition) by four (assessment point) factorial design. All participants will complete an assessment battery at baseline (T1: recruitment), immediately after participation in Cascade or the PSG control (T2), 5-weeks post-intervention/1-week post-booster session (T3), and 6-months post-intervention (T4). The waitlist group will be assessed at the same time points. After the 6-month waitlist period, waitlisted parents will be re-randomised to either Cascade or the PSG. They will complete a final, additional, assessment battery immediately after their group program (T5). All the children ages 7 to 15 years of participating parents (including the child cancer survivor and any siblings) will be invited to complete measures of depression, anxiety and peer relationships at the same time points as their parents (see Table 1).

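### If the random-intercept model covers all four visits with independent residuals, it assumes one correlation for very unequal intervals and can misstate the error of the T1–T2 and T1–T4 contrasts

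*Protocol article*

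**What the plan says.** Statistical analyses: group differences in QoL change are to be estimated with mixed random-intercept models. The T1–T2 contrast is named as primary, and T1–T3 and T1–T4 follow in the same sentence. The reason given for the model is that "Random intercept models, which utilise maximum-likelihood estimation, provide more efficient estimates of effects with unbalanced data". No residual covariance structure, random slope or robust standard error is named. The section does not say whether one model is fitted to all four visits or a separate model to each pair.

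Methods/Design: "This study employs a three (treatment condition) by four (assessment point) factorial design". After baseline (T1) and the assessment straight after the programme (T2), the later assessments are "5-weeks post-intervention/1-week post-booster session (T3), and 6-months post-intervention (T4"). Participant recruitment puts the first questionnaire 2 weeks before Week 1, and Procedures puts the sessions in Weeks 1 to 4.

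Participants: the sample size is about 40 per arm "with a power of 80% at a two-tailed significance level of 0.05", taking "d = 0.65 as the difference in change from time 1 to time 2 for any pair of groups".

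**The concern.** In its ordinary form, a random-intercept model has independent residuals of constant variance. That is compound symmetry: equal variance at every visit and one correlation for every pair. Every change from baseline then gets the same standard error, built from a single within-parent variance pooled over four visits.

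The visits are far from equally spaced. T1–T2 covers about 6 weeks (2 weeks before Week 1 to the end of Week 4). T1–T4 covers about 32 weeks, or 7 months (those 6 weeks plus about 26). Repeated QoL scores often correlate less as the gap grows. The article's own Discussion expects parents to differ over the 6-month follow-up in the services and peer contact they receive.

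If the correlation does change with the gap, the pooled variance is wrong for individual contrasts. At stake are the power of the primary comparison and the error rate of the 6-month comparison. Under some patterns the error rate of the primary comparison is at stake too.

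**Working it through.** **1. The plan's own figure.** Inputs from Participants: d = 0.65, two-sided alpha 0.05, 80% power. The normal approximation gives 38 per arm and the two-sample t test 39, against 40 planned. Power at 40 per arm is 82.8% (normal) or 81.9% (t). Recruitment also reproduces: 375 × 0.40 × 0.80 = 120. The stated sample size is sound, with little reserve.

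**2. Formula.** Take complete data, 40 per arm and unit variance at each visit. The random-intercept estimate is then the plain difference in mean change. Only its standard error depends on the covariance model.
- Pooled within-parent variance: s² = 1 − (mean of the six pairwise correlations).
- Change variance the model uses: 2s² for every contrast.
- True change variance for T1–Tj: 2(1 − r1j).
- Ratio of model SE to true SE: k = √[2s² / 2(1 − r1j)].
- Actual type I error at nominal 5%: 2[1 − Φ(1.96k)].
- Power for T1–T2, with d on the SD of change: Φ(0.65√20 − 1.96k), where 0.65√20 = 2.907.

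**3. Two examples.** All correlations are assumptions, because the article gives none.
- Moderate decay (r12 = 0.75, r14 = 0.50, mean of all pairs 0.64): s² = 0.36. T1–T2: k = √(0.72/0.50) = 1.20, type I error 1.9%, power Φ(2.907 − 2.352) = 71%. T1–T4: k = √(0.72/1.00) = 0.85, type I error 9.6%.
- Low baseline correlation (0.50 with each later visit; later visits 0.75, 0.65 and 0.70 with each other): mean 3.60/6 = 0.60, s² = 0.40, k = √(0.80/1.00) = 0.894. Type I error is 8.0% for all three contrasts.

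**4. Range.**

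| Assumed pattern | r12, r14 | T1–T2 type I | T1–T2 power | T1–T4 type I |
|---|---|---|---|---|
| Equal correlation | 0.60, 0.60 | 5.0% | 82.8% | 5.0% |
| Mild decay | 0.70, 0.60 | 3.7% | 79.4% | 7.1% |
| Stable part plus decaying part | 0.70, 0.50 | about 2.3% | 73.4% | 7.6% |
| Moderate decay | 0.75, 0.50 | 1.9% | 71.1% | 9.6% |
| Continuous-time decay to near zero | 0.70, 0.15 | 0.7% | 58.6% | 11.0% |
| Low baseline correlation | 0.50, 0.50 | 8.0% | not comparable (inflated test) | 8.0% |

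Continuous-time decay with r12 from 0.5 to 0.9 spans 1.6% to 0.2% at T1–T2 and 8.6% to 14.0% at T1–T4. These are extreme cases. All rates are per contrast at nominal 5%, before the planned Holm-Bonferroni adjustment.

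**5. Simulation check.** Three arms of 40 and four visits, 20,000 runs. Equal correlation gave 4.8% (T1–T2) and 4.9% (T1–T4). Continuous-time decay with r12 = 0.7 gave 0.7% and 11.1%. A separate simulation of moderate decay (8,000 null trials) gave 1.9% and 9.4% with the random intercept, and 5.1% and 4.8% with an unstructured covariance. An analysis of T1–T2 change alone gave 4.8–5.0%.

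**6. Scaling of d.** The article standardises d on a pooled within-group SD and does not say whether this is the SD of change or of scores. If it is the SD of scores, r12 = 0.75 makes the SD of change √0.50 = 0.707, so d on that scale is 0.65/0.707 = 0.919. Power is then Φ(4.11 − 1.96) = 98%, falling to Φ(4.11 − 2.35) = 96% under moderate decay.

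**The case against.** A reader might infer that the plan fixes a random intercept and nothing else, that the T1–T4 test is therefore anti-conservative, and that the primary test necessarily loses power. The documents do not support that much.

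- **Residual structure.** The text does not exclude a structured residual added to the intercept, and a journal article may leave that detail to the full plan.
- **One model or several.** The section speaks of models in the plural and lists three changes. If each is fitted to its own two visits, complete-data inference reduces to a change-score comparison and the problem disappears for every contrast. A T1–T4 analysis fitted that way with r = 0.5 gave 5.1% in simulation.
- **Direction.** No between-visit correlation or variance is given. Equal correlation does no harm, and the low-baseline pattern reverses the direction for the primary contrast.
- **Power.** The loss matters only if d is scaled on the SD of change.
- **Stakes.** Both efficacy hypotheses under Aims and hypotheses concern T1 to T2. Under decay that test is conservative, so no false-positive primary claim follows. The inflated T1–T4 contrast carries no stated hypothesis.
- **The efficiency statement.** As a comparison with traditional repeated measures it is not false. The commitment lies in the sentence before it.

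All of this stands, and it makes the point conditional. It does not remove it. The model is named twice and given its own justification, its ordinary meaning is compound symmetry, and nothing in the section says that pairs of visits are analysed separately.

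**Conclusion.** The concern holds conditionally. If one random-intercept model with independent residuals is fitted to all four visits, its error rates are right only when the variances and correlations meet its equal-correlation assumption, or happen to average out for the contrast in question.

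- **Mild to moderate decay:** T1–T2 type I error of about 4% down to 2%, with power from about 82% to about 79–71% if d is on the SD of change. T1–T4 type I error is about 7–10%. Steeper decay goes beyond these ranges.
- **Low baseline correlation:** about 8% for all three contrasts, including the primary.
- **Equal variance and correlation:** no error.

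The figures assume complete data, 40 per arm and equal variance over visits. The documents cannot show which pattern applies. The case for a change is that a method holding the error rate under all of these patterns is available at little cost. It is not that the stated model has been shown to fail.

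**What to change.** In Statistical analyses, replace the random-intercept wording with a mixed model that has visit as a factor, arm-by-visit terms and an unstructured 4x4 within-parent covariance, estimated by REML with Satterthwaite degrees of freedom. Name a fallback for non-convergence, such as heterogeneous Toeplitz. Compound symmetry is a special case of the unstructured form, so the choice protects the error rate whichever pattern holds, and all available visits still contribute.

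Alternatively, state that each contrast is fitted to its own two visits.

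The cost is a change of wording and ten covariance parameters (4 variances and 6 covariances) instead of two, which is estimable with about 120 parents. Recruitment and data collection do not change.
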